| Technical Summary (Max. 300 words) *Background*  The population is ageing and consequently, the number of people living with age-related chronic conditions is increasing. Polypharmacy (five or more prescribed medications) is common in older people and is associated with an increased risk of adverse drug reactions. Preventative medications, such as those used to manage blood pressure and cholesterol, are common in polypharmacy and often require large numbers of people to be treated to prevent a small number of cardiovascular disease (CVD) events. This leaves many individuals on drugs of little benefit, some of whom may be susceptible to side effects such as falls, kidney problems and muscle pain.  *Aims*  This proposal aims to quantify the harms of cardiovascular prevention medication, and the characteristics of those people most likely to suffer them. This research is one part of a larger research programme to develop a clinical decision tool which estimates an individual’s likelihood of benefiting or suffering harm from treatment.    *Methods*  Aim 1: Derive prognostic models for an individual’s risk of adverse events associated with cardiovascular prevention treatment (antihypertensives, statins and antiplatelets) using data from the CPRD GOLD. Adverse event outcomes will include falls (antihypertensives), myopathy (statins) and bleeding (antiplatelets).  Aim 2: Externally validate each model using data from the CPRD Aurum.  Aim 3: Use causal inference methods (propensity score matching, instrumental variable analysis) to examine whether modification of treatment could have an important impact on the risk of adverse events. |

| Outcomes to be measured **Primary outcomes** - Falls; Myopathy/muscle pain; Intracerebral haemorrhage  **Secondary outcomes** – Fracture; Syncope; Hypotension (symptomatic); Acute kidney injury; Electrolyte abnormalities; Gout; Diabetes mellitus; Intracerebral haemorrhage; Cataract; Liver dysfunction; Dementia; Memory problems (including dementia); Gastrointestinal haemorrhage; Dyspnoea; Any adverse event  Specific outcomes will be examined in relation to exposure to either antihypertensives, statins or antiplatelets (details given in section N). |
| --- |

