| Planned use of linked data (if applicable): Data linkage to the ONS and Basic HES are required to define the primary and secondary outcomes in the study. The ONS mortality register will be used to define any outcomes which result in death, and also censor follow-up at death. Specific linkages required will include data and ICD-10 coded cause of death (see attached code lists). Linkages to Basic Inpatient HES will be combined with data from the ONS to define all other outcomes in the study. HES data will also be used to define patients’ eligibility for the study (e.g. previous CVD), and define the study population (e.g. ethnicity where unavailable in Primary Care records). Data required from Basic Inpatient HES will include primary diagnosis, secondary diagnosis, patient characteristics (e.g. sex, ethnicity), date of admission and date of discharge. All deaths and hospital admissions occurring after a patient’s index date will be included. A linkage to the Index of Multiple Deprivation is required to acquire patient level quintiles of multiple deprivation, to better define the sample population and use as a covariate in the prognostic modelling. |

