| Definition of the Study population Individual patient data will be extracted from the medical records of all patients registered at linked general practices contributing to the CPRD GOLD and Aurum in England.  Patients will be included if they meet the following criteria:   - Patients over the age of 40 years - Registered to a CPRD ‘up-to-standard’ practice - Records available after the study start date (01/01/1998) - Sufficient data to define the index date (see table below)   Patients will be excluded if they meet the following criteria:   - Previous prescription of the exposure variable (antihypertensive, statin or antiplatelet) - Blood pressure >180 mm Hg or total cholesterol >7.5 mmol/L (in patients with high blood pressure or cholesterol, treatment is indicated regardless of risk)   Study entry criteria – Patients will enter the cohort on the index date, defined as:   \| **Exposure** \| Antihypertensive therapy \| Statin therapy \| Antiplatelet therapy \| \| --- \| --- \| --- \| --- \| \| **Index date definition** \| 12 months after the first systolic blood pressure reading ≥130 mm Hg \| 12 months after the first coded or calculated CVD risk of ≥5% \| 3 months after first CVD event \|   Study exit criteria   - Last date at which the most recent linked data are available from the CPRD (study end date, July 2018) - Date of the most recent data upload from the practice to which a given patient is registered - Date at which a given patient transfers out of a registered CPRD practice - Date of death or specific outcome of interest |
| Selection of comparison group(s) or controls Aim 1: Not applicable – single cohort in CPRD GOLD.  Aim 2: Not applicable – single cohort in CPRD AURUM.  Aim 3 will use propensity score matching and instrumental variable analysis – see Methods section below. |

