| Exposures, Outcomes and Covariates This study will examine the overall risk of harm from three types of cardiovascular medication: antihypertensives, statins and antiplatelets. ‘Harm’ will be defined by the outcomes listed in the table below, which will be examined both individually and as a composite outcome. The association between treatment and a positive and negative control outcome will also be examined to check the validity of the treatment effect estimates. Positive controls are outcomes know to be affected by treatment (e.g. cardiovascular disease) and negative outcomes are those known not to be affected by treatment.   \| **Variable** \| **Antihypertensive therapy** \| **Statin therapy** \| **Antiplatelet therapy** \| \| --- \| --- \| --- \| --- \| \| Exposure \| ACE inhibitors  Angiotensin II receptor antagonists  Calcium channel blockers  Thiazides and thiazide-like diuretics  Beta blockers  Alpha blockers  Centrally acting antihypertensives  Vasodilators  Renin inhibitors \| Statins \| Aspirin  Clopidogrel  Dipyridamole  Ticagrelor  Prasugrel \| \| Outcome (hospital admission or death due to) \| Falls  Fracture  Syncope  Hypotension (symptomatic)  Acute kidney injury  Electrolyte abnormalities*  Gout  Any adverse event \| Myopathy/muscle pain  Diabetes mellitus  Intracerebral haemorrhage  Cataract  Liver dysfunction  Dementia  Memory problems (including dementia)  Any adverse event \| Intracerebral haemorrhage  Gastrointestinal haemorrhage  Dyspnoea  Any adverse event \| \| Covariates (predictors of outcome and/or treatment) \| Age, sex, BMI, blood pressure, cholesterol, HbA1c, other prescribed medications, co-morbidities, social deprivation, previous adverse events, frailty and proximity to death. \| \| \|   *Defined as any (hyponatraemia, hypokalaemia, hyperkalaemia, hypomagnesaemia, hypophosphataemia hypercalcaemia or hyperuricemia)  All outcomes will be defined according to diagnostic and/or symptom codes, unless otherwise stated. Further sensitivity analyses will explore the impact of our definition of myopathy and muscle pain, focussing on formal diagnostic codes for myopathy only.  Our PPI engagement suggests some patients are concerned about side effects which will result in having to go to hospital, whilst others are more concerned about chronic conditions which affect their daily quality of life. The primary outcomes of this study will therefore be hospital attendance, defined according to ONS and Basic HES datasets. Sensitivity analyses will explore outcomes defined more broadly using primary care codes as well.  All published outputs from this work will be based on the outcomes as specified in this application. Further work with our patient and public involvement representatives will explore definitions of these outcomes and how they should be incorporated into the final calculators developed as part of the wider programme of work related to this project.  Each model will be derived pragmatically, using coded data routinely available in a primary care setting. Potential predictors will be selected based on previous literature and expert opinion.^30 31 44^ Predictors will be defined by codes in the primary care records, using code lists from previous studies (via [www.clinicalcodes.org](http://www.clinicalcodes.org)). Each model will also incorporate basic patient characteristics, blood pressure level, co-morbidities and frailty, estimated from the electronic frailty index. |

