| List of Appendices Appendix 1. Code lists for the primary outcomes |
| Amendments **Amendment 1 – 19/05/2019 (approved)**  **We clarify that aims 1 and 2 (prognostic model derivation and validation) of the study should include the whole population independently of whether patients are new or old users of preventative treatment; the causal inference analyses will focus on new users only:**  *L. Definition of the study population*  Patients will be excluded if they meet the following criteria:  Previous prescription of the exposure variable (antihypertensive, statin or antiplatelet; for causal inference analyses only)  **Amendment 2 – 28/06/2021 (approved 05/07/2021)**  **We have made the following revisions aimed at simplifying the analysis plan in light of the very large sample size and computational time required to conduct each analysis:** *C. Technical Summary / E. Objectives, Specific Aims and Rationale* Aims:  3) Use causal inference methods (multivariable regression, propensity score adjustment/matching, instrumental variable analysis) to examine whether modification of treatment could have an important impact on the risk of adverse events.  *L. Definition of the study population*  Study entry criteria – Patients will enter the cohort on the index date, defined as:   \| **Exposure** \| Antihypertensive therapy \| Statin therapy \| Antiplatelet therapy \| \| --- \| --- \| --- \| --- \| \| **Index date definition** \| 12 months after the first systolic blood pressure reading ≥130 mm Hg \| 12 months after the first coded or calculated CVD risk of ≥5% (equivalent to age ≥50 years for men and ≥60 years for women) \| 3 months after first CVD event \|   *N. Exposures, Outcomes and Covariates*  Positive controls are outcomes know to be affected by treatment (e.g. cardiovascular disease, death)  For causal inference analyses (only), sensitivity analyses will explore outcomes defined more broadly using primary care codes as well. *O. Data/ Statistical Analysis* We no longer plan to conduct an internal validation of the prediction models. The following text from the protocol is therefore redundant:  Where feasible and appropriate, each model will be internally validated using the bootstrap method, to allow optimism-adjusted estimates of calibration and discrimination performance to be obtained. Adjustment for overfitting will be undertaken using a uniform shrinkage factor identified from bootstrapping, followed by re-estimation of the cumulative baseline sub-distribution hazard function (and thus baseline cumulative incidence function) to maintain overall calibration between observed and predicted risks. Given the large sample size, overfitting is likely to be small (see sample size calculation above). If bootstrapping is computationally infeasible due to the large sample size, then a smaller random sample of the population will be used or alternative internal validation methods employed such as cross validation.  *Aim 3 – causal inference analysis*  For most of the outcomes described in this proposal, the association and magnitude of effect with treatment is not well defined in randomised controlled trials. We will therefore undertake causal inference work to examine whether modification of treatment could have an important impact on the risk of adverse events using two causal inference methods: multivariable adjustment, propensity score adjustment/matching and instrumental variable analysis.  For the analysis using multivariable adjustment, Cox proportional hazards models will be used to compare adverse event rates in each experimental group. Estimates will be adjusted for pre-specified variables thought to confound the relationship between treatment and adverse events.  For the analysis using propensity scores, we will conduct separate analyses adjusting for propensity score and matching via propensity score.  *Subgroup and sensitivity analyses*  Where possible and appropriate, analyses of treatment associations will be examined in subgroups of the population. These will include age, sex, baseline blood pressure and cardiovascular risk, by drug type/dose/intensity and past medical history. Subgroup definitions will be agreed by expert opinion or taken from an accompanying systematic review of previous trials, examining the same topic. For computational reasons (whereby only one imputation model is required for all subgroup analyses of each outcome), these analyses will only be undertaken using propensity score adjustment. *P. Plan for addressing confounding* Two approaches will be taken to determine whether observed associations are potentially subject to residual confounding.^46^ Where all approaches provide similar results, we can be more confident that the findings are accurate and reliable. Further steps will be taken to examine the validity of treatment effect estimates using positive and negative controls: the impact of treatment on an outcome known to be affected by treatment (e.g. cardiovascular disease and death; positive controls)  **Amendment 3 – 25.11.2021**  **We have added exploratory analyses using supervised machine learning approaches to address missing data and deal with confounding by indication in the causal inference analyses.** O. Data/ Statistical Analysis ***Aim 3 – causal inference analysis***  For most of the outcomes described in this proposal, the association and magnitude of effect with treatment is not well defined in randomised controlled trials. We will therefore undertake causal inference work to examine whether modification of treatment could have an important impact on the risk of adverse events using two causal inference methods: propensity score matching and instrumental variable analysis.  For the propensity score analysis, eligible patients will be matched 1:1 at the index date using propensity scores, which indicate the likelihood a patient will be prescribed treatment on the basis of their known (pre-treatment) characteristics and other known information which might influence the decision to treat. Predictors of preventative drug prescription will be explored in a logistic regression model. Matched patients will be compared using the Cox proportional hazards models, but hazard ratios will only be adjusted by factors unbalanced at baseline which are not already included in the propensity score model. Time since cohort entry will be used as the underlying time function in each model.  For the instrumental variable analysis, GP’s previous antihypertensive prescribing preferences will be used as an instrument to predict the likelihood of actual treatment. Risk of adverse events will be estimated in patients attending a GP considered a high prescriber of preventative medication and compared to those attending a GP considered a low prescriber. If the results from the propensity score matching suffer from unmeasured confounding, they will differ from those of the instrumental analysis. If this is the case, these models will be refined with additional factors to achieve better adjustment and matching. Where all approaches provide similar results, we can be more confident that the findings are accurate and reliable.^46^  Generative Adversarial Networks (GAN) will also be used to impute missing counterfactual data (unobserved effects of untaken treatments) on an individual level. GAN models are a class of machine learning frameworks that involves the simultaneous training of a pair of deep neural networks in competition with each other. The idea is that the first network, the generator, generates synthetic data samples that are similar to the original samples, while the second network, the discriminator, evaluates the authenticity of the generated samples [1]. Data similarity and fidelity are usually evaluated using well-known metrics such as Maximum Mean Discrepancies [2] and Jensen-Shannon Divergence [3]. While GAN’s initial uses were for imaging applications, its generative capabilities make it naturally suitable for generating missing values that can be used to impute the original samples.  In this work, we build on the intuition that treatment effects estimation and causal inference are a missing data problem, where counterfactuals (unobserved effects of untaken treatments) are missing [4]. Specifically, we plan to use GAN to impute missing counterfactual data, for the samples available in CPRD. By modifying the generator’s goal to accurately impute missing data, and the discriminator’s goal to distinguish between observed and imputed counterfactual values for the same patient record. The model can generate the missing data conditional on the observed values and assigned treatment for each patient as seen in [5, 6]. While useful, the work of [5, 6] are not compatible for time-series data nor for estimating multiple treatment effects, which limits its use in real-life treatment applications. Therefore, we plan to extend such previous works to make them compatible for multiple treatment options and for time-series data to allow for long-term treatment (antihypertensives, statins, antiplatelets) estimation effects for multi-morbid populations as initially proposed in this project.  The proposed GAN approach does not generate new patient samples, but rather generates counterfactual (missing component) conditioned on observed factual data, and outputs a complete record with both factual and counterfactual outcomes to allow for treatment effect estimation for each patient. This approach is naturally immune to re-identification attacks since no new samples are generated, but we will run privacy checks and measures within the data to verify that the model is not copying potential outcomes from patients in the training sample. Example privacy measures that we plan to apply include empirical evaluations such as mathematical privacy definitions such as identifiability [7] that quantifies the probability of re-identification to ensure that no combination of attributes could reveal the identity of a patient. Other privacy evaluation methods include testing that the model is robust against membership inference attacks, where an attacker attempts to determine if a specific patient was used in the training set of the model [8]. Lastly, we will experiment with strict theoretical guarantees such as differential privacy which allow for the model to learn almost nothing about an individual while learning useful information about a population [9].  **References**  [1] Ian Goodfellow, Jean Pouget-Abadie, Mehdi Mirza, Bing Xu, David Warde-Farley, Sherjil Ozair, Aaron Courville, and Yoshua Bengio. Generative adversarial nets. *Advances in neural information processing systems*, 27:2672–2680, 2014.  [2] Arthur Gretton, Karsten M Borgwardt, Malte J Rasch, Bernhard Sch¨olkopf, and Alexander Smola. A kernel two-sample test. *The Journal of Machine Learning Research*, 13(1):723–773, 2012.  [3] AP Majtey, PW Lamberti, and DP Prato. Jensen-shannon divergence as a measure of distinguishability between mixed quantum states. *Physical Review A*, 72(5):052310, 2005.  [4] Peng Ding and Fan Li. Causal inference: A missing data perspective. *Statistical Science*, 33(2):214– 237, 2018.  [5] Jinsung Yoon, James Jordon, and Mihaela Schaar. Gain: Missing data imputation using generative adversarial nets. In *International Conference on Machine Learning*, pages 5689–5698. PMLR, 2018.  [6] Jinsung Yoon, James Jordon, and Mihaela van der Schaar. Ganite: Estimation of individualized treatment effects using generative adversarial nets. In *International Conference on Learning Representations*, 2018.  [7] Jinsung Yoon, Lydia N Drumright, and Mihaela Van Der Schaar. Anonymization through data synthesis using generative adversarial networks (ads-gan). *IEEE journal of biomedical and health informatics*, 24(8):2378–2388, 2020.  [8] Reza Shokri, Marco Stronati, Congzheng Song, and Vitaly Shmatikov. Membership inference attacks against machine learning models. In *2017 IEEE Symposium on Security and Privacy (SP)*, pages 3–18. IEEE, 2017.  [9] Cynthia Dwork, Aaron Roth, et al. The algorithmic foundations of differential privacy. *Found. Trends Theor. Comput. Sci.*, 9(3-4):211–407, 2014.  **Amendment 4 – 30.11.2022**  **Added University of Birmingham to the list of data processors.** |

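### Patients who already have diabetes, dementia, memory problems or cataract at index stay in the risk set for that same secondary outcome, so old disease can be counted as new harm

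*Protocol*

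**What the plan says.** - **Outcomes.** The protocol's section Outcomes to be measured lists among the secondary outcomes "Gout; Diabetes mellitus; Intracerebral haemorrhage; Cataract; Liver dysfunction; Dementia; Memory problems (including dementia". In the table under Exposures, Outcomes and Covariates, diabetes, cataract, dementia and memory problems are statin outcomes, together with a composite of any adverse event.
- **Definition.** The row label of that table is "Outcome (hospital admission or death due to", and the text below it adds "All outcomes will be defined according to diagnostic and/or symptom codes, unless otherwise stated". Nothing requires a first-ever record. The same section commits published outputs to the outcomes as specified in the application.
- **Data fields.** Planned use of linked data says "Data required from Basic Inpatient HES will include primary diagnosis, secondary diagnosis", and that all deaths and admissions after the index date are included. It does not say which diagnosis position makes an admission an outcome.
- **Eligibility.** Definition of the Study population introduces its list with "Patients will be excluded if they meet the following criteria" and gives two items: "Previous prescription of the exposure variable (antihypertensive, statin or antiplatelet" and "Blood pressure >180 mm Hg or total cholesterol >7.5 mmol/L". Amendment 1 edits the first item to "Previous prescription of the exposure variable (antihypertensive, statin or antiplatelet; for causal inference analyses only" and adds nothing on existing outcome disease.
- **Prior disease.** Co-morbidities and previous adverse events appear in the covariate row, so these patients are kept and modelled.

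**The concern.** Diabetes, dementia and cataract are long-standing conditions. A patient who has one at index cannot develop it during follow-up, yet a later admission that meets the definition would be scored as an adverse event of treatment.

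Two products of the study are exposed. In Aim 3, events in existing cases say nothing about whether the drug causes the condition, so they dilute the hazard ratio. In Aims 1 and 2 there is no comparison group, and the predicted 10-year risk becomes a mixture of developing the disease and having old disease coded. The protocol intends these results to feed a freely available online calculator, where such a number would be read as the risk of harm. The plan is powered for a 10% increase in rate, which leaves little room for dilution.

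**Working it through.** **The plan's own figure.** The Sample size considerations section asks for 4,634 events and 88,380 patients for the causal analyses: a 10% increase in rate, 0.5% per year in the unexposed, 90% power, alpha 0.05. Freedman's formula for 1:1 groups, two-sided, gives

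(1.960 + 1.282)² × (2.10/0.10)² = 10.507 × 441 = 4,634 events.

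Over 10 years the control risk is 5% and the treated risk is 1 − 0.95^1.1 = 5.486%, mean 5.243%. Then 4,633.8/0.05243 = 88,380. Both figures reproduce, so the arithmetic is sound. The formula takes every counted event to carry the 10% effect, and events in existing cases do not.

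**Inputs for the size of the dilution**
- From the protocol's sample size section: hazard ratio 1.10; incidence *i* = 0.5% per year as the lower value; *T* = 7 years (the median follow-up used there for intracranial haemorrhage).
- Assumed, because the documents give no figure: prevalence at index *p* = 10%, equal in both groups; upper incidence 1% per year; yearly rate *h* at which an existing case has a qualifying admission. For *h*, 0.5-2% represents admission due to the condition, and 5-15% represents a secondary code at any admission.
- Assumed: treatment does not change *h*.

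**Formulas**
- Existing-case events: A = p(1 − e^(−hT))
- New-case events: B = (1 − p)(1 − e^(−iT))
- Share of events from existing cases: s = A/(A + B)
- Diluted hazard ratio (approximate): exp[(1 − s) ln 1.10]

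| Reading of 'due to' | h | i | A | B | s | Diluted HR |
|---|---|---|---|---|---|---|
| Admission due to the condition, low end | 0.5% | 1% | 0.0034 | 0.0609 | 5% | 1.09 |
| Admission due to the condition, high end | 2% | 0.5% | 0.0131 | 0.0310 | 30% | 1.07 |
| Any secondary code, low end | 5% | 1% | 0.0295 | 0.0609 | 33% | 1.07 |
| Any secondary code, high end | 15% | 0.5% | 0.0650 | 0.0310 | 68% | 1.03 |

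Applying 1.10 directly to the new-case hazard and recomputing the mixture gives 1.094, 1.071, 1.068 and 1.033, so the approximation is adequate.

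**Absolute risk.** With i = 0.5% per year, the 7-year risk in people free of the condition is 1 − e^(−0.035) = 3.4%. The average counted risk, A + B, is 4.4% at h = 2% and 9.6% at h = 15%. At the mildest corner (h = 0.5%, i = 1%) it is 6.4% against a true 6.8%, so the error need not be upward.

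**Sensitivity to prevalence.** On the plan's 10-year, 5% risk, assume prevalence of 2-15% and a 10-60% chance overall that old disease is coded. Old disease is then 4-68% of events and the hazard ratio 1.096-1.034. At 5% prevalence and 30% coding the figures are 24% and about 1.08, and power at exactly 4,634 events is about 71%.

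**The case against.** **The outcome is an admission due to the condition.** A reader might infer that any secondary code at any later admission makes an existing case an event. The documents do not say so. The linked-data section lists fields to be requested, and the same hospital data also serve eligibility. This objection stands and limits the size. It does not remove the problem, because an admission due to long-standing diabetes, dementia or cataract still counts.

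**The analysis adjusts for prior disease.** A reader might infer that unequal prevalence would create a spurious treatment effect. Unadjusted, it could: 12% against 8% prevalence, with h = 10% and i = 0.5%, gives a risk ratio of about 1.26 under no effect. The plan, however, specifies multivariable adjustment, propensity score methods and an instrumental variable analysis, with co-morbidities and previous adverse events as covariates. Imbalance between groups is therefore largely addressed, and that figure should not be attached to the planned analysis. Dilution and the meaning of the absolute risk are not addressed, since adjustment does not make an existing case a new one.

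**Not every listed condition behaves this way.** Gout and liver dysfunction can produce a genuine new episode. With gout set aside, the argument does not carry into the antihypertensive composite.

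**It could be left to the analysis plan.** Look-back windows and code lists commonly are. Who is eligible is fixed in this protocol, however, and its text keeps these patients.

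**Conclusion.** The point holds for diabetes mellitus, dementia, memory problems (including dementia) and cataract, and for the statin composite that contains them. It holds under either reading of 'due to'; only the size changes. On the assumptions above, existing cases are about 5-30% of events under the narrow reading and about 33-68% under the broad one, and a hazard ratio of 1.10 becomes about 1.09-1.07 or 1.07-1.03. Prevalence, admission rates and diagnosis position are not in the documents, and at low prevalence with little recoding the effect is near negligible (4% of events, 1.096).

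A reader might also infer that the primary results are compromised. They are not: falls, myopathy or muscle pain, and intracerebral haemorrhage are largely acute or recurrent, and the protocol gives them reporting priority. This is a correction that should be made to secondary outcomes.

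**What to change.** 1. For diabetes, dementia, memory problems and cataract, exclude from that outcome's analysis, in both GOLD and Aurum, patients with a primary care or hospital record of the condition before the index date.
2. In the statin any-adverse-event composite, count each of these components only in patients free of it at index.
3. State which hospital diagnosis position makes an admission due to the condition.
4. For gout and liver dysfunction, prior disease can remain a covariate.

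The cost is one eligibility sentence per outcome, one sentence on diagnosis position, and a modest loss of patients from those analyses, in a study expecting about 3.3 million.
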